*** Other outcomes***					
	Thalamus length, width, and transverse	Continuous (in cm)	Ultrasound measurement	Between 20–26 weeks and 30–34-week gestational ages	Mean (SD)
	Consumption of ASF	Score (0–4)	Based on DQQ questionnaire	Between 9– < 14 weeks, 20–26 weeks, and 30–34 weeks of gestational ages, at time of birth, and at 6-week and 6-month post-birth	Mean (SD)
	Child’s motor, cognitive, socio-emotional, and language development domain specific scores	Domain-specific scores	Based on CREDI long form	6 months of age	Mean (SD)

### Participant timeline {13}

Women will be recruited during the first trimester of pregnancy and will be asked to plan to remain in the study until the child is 6 months of age. Women will engage in study visits at the health center during the first (enrollment), second, and third trimesters of pregnancy. Additional follow-ups will be conducted at the time of birth (within 72 h) and when the child is 6 weeks and 6 months of age at the health facility. In addition, after enrollment, all participants will be asked to come to the CHW house every day to receive IEC messaging and eggs (intervention group only). Table 2 details participants’ timeline and assessments for the study.

**Table 2 Tab2:** Timeline of enrollment, intervention, and data collection from *Deux Oeufs* participants

	**During pregnancy**			**Birth**	**Post-birth follow-up**	
**Timepoint**	**GA (9– < 14 weeks)**	**GA (20–26 weeks)**	**GA (30–34 weeks)**	**Within 72 h**	**6 weeks**	**6 months**
**Enrollment**						
Eligibility screen	X					
Informed consent	X					
**Intervention**						
Two eggs supplement (treatment group)	X	X	X	X		
Daily health messages (treatment group and control group)	X	X	X	X		
**Assessments**						
Ultrasound assessment	X	X	X			
Blood sample collection (women) and assessment (RBC, Hemoglobin, cholesterol, MCV, and platelets)	X	X	X		X	X
Blood sample collection (infant)					X	X
Hair sample collection (mother)	X	X	X		X	X
**Baseline and follow-up surveys**						
Mother’s anthropometry	X	X	X	X*	X	X
Mother’s clinical assessment (blood pressure and current health condition)	X	X	X			
Mother’s medical and obstetrics history	X					
Socioeconomic status	X					X
Smoking and alcohol consumption	X	X	X		X	X
Dietary Quality Questionnaire (DQQ)	X	X	X		X	X
Household Food Security (HFIAS)	X					X
Water and sanitation	X					
Pregnancy history	X					
Malaria prevention	X					
Physical activity	X	X	X			
Depression (EPDS)		X	X		X	X
Intention to breastfeed		X	X			
Immediate feeding				X		
Gender-based violence					X	X
**Outcomes**						
Child anthropometry				X	X	X
Child health status and medical history after birth			X		X	X
HNNE					X	
Child development (CREDI)						X
Infant feeding practices				X	X	X
Maternal biomarkers	X	X	X			
Child biomarkers					X	X
*< 1 week before birth						

### Sample size {14}

Nutritional interventions during pregnancy have yielded mixed results in their impact on LAZ at birth. Previously reported mean difference in LAZ ranges from 0.12 [2, 18] to 0.29 [12, 17]. Notably, the 0.29 effect size observed by Dhaded et al. [12] was associated with nutritional supplementation initiated prior to conception, whereas supplementation beginning in the first trimester yielded a smaller effect size of 0.21. Considering most studies report an effect size below 0.20 and based on the available literature on other food supplementation as found in some literature review papers by Imdad and Bhutta [23] and Stevens et al. [46], we hypothesize a mean difference of 0.18 in LAZ to be both a reasonable and clinically meaningful effect size. As such, we calculate the sample size based on testing two hypotheses simultaneously:$$H0:d1\leq0\;vs.\;Ha:d1>0$$

For our hypothesized effect size, the sample size required with 20% attrition (accounting for pregnancy loss, stillbirths, and loss of follow-up) to attain an 80% marginal power with a 5% level of significance was 478 per arm, based on a two sample one-sided test. Thus, we aim to enroll an overall sample of 956 women in the proposed study. Sample calculation was performed using “pwr” package [5] in RStudio.

### Recruitment {15}

Before enrollment begins and during the entire study period, study staff will organize educational and informational campaigns in villages within the catchment area to promote early antenatal care (ANC) visits and facilitate visits to health centers. This is necessary in order to identify eligible women within the first trimester of pregnancy. CHWs and other identified community champions will encourage women in the village who are of childbearing age to attend ANC visits as soon as they suspect or confirm they are pregnant. Formative research indicated that many women delay health-seeking behavior around pregnancy until they have a high level of confidence that they are pregnant. Study staff, together with CHWs, will also raise awareness of the symptoms of early pregnancy and about the study in general through sector social affairs officers, cell-level officials, and village chiefs and by posting informational posters at health centers, health posts, and other appropriate locations. Urine-based pregnancy tests will be distributed to CHWs to encourage discrete/private confirmation of suspected pregnancy and attendance at a first antenatal care visit as early as possible. Study personnel will work with CHWs who keep a roster of all pregnancies in the village. CHWs will identify potential participants in their first trimester and encourage them to visit the health center for the study. At the commencement of the study, staff will coordinate with CHWs to compensate transportation costs for women with positive pregnancy tests from the village to the health care center serving the catchment area. The study staff will be available at the health center to conduct standardized screening ultrasounds and gather baseline data. Women who present at the health center for an ANC visit without referral from a CHW may also engage in the screening and enrollment process previously described.

For ultrasound screening, a portable handheld ultrasound system that combines GE VScan Air with the IntelligentUltrasound artificial intelligence-enabled ScanNav FetalCheck (Cardiff, Wales) will be used to date pregnancies. Pregnancy will be dated using ScanNav FetalCheck. If a FetalCheck is unable to provide a measure (typically < 10-week gestation), crown-rump length (CRL) will be used to date pregnancy in conjunction with the reported last menstrual period based on standard methods and INTERGROWTH 21st standards. Once eligibility is confirmed, participants provide informed consent before enrollment and assessment during an initial study visit.

Participants will be asked to visit their health center according to a normal ANC visit schedule. At two of these ANC visits, the participants will be examined and surveyed by our study team: one at 20–26 weeks and another at 30–34 weeks. The study staff will provide an approximate appointment date for these visits, and participants will be reminded of the same by phone in the days leading up to their second and third trimester visits.

## Assignment of interventions: allocation

Following enrollment, women will be randomly allocated to the control arm or the intervention arm by selecting an envelope of their choice from three options.

### Sequence generation {16a}

The study will apply stratified block randomization with varying block sizes to randomly assign the treatment arms and to preserve the balance of treatment across gestational age groups (9–11 weeks and 12 < 14 weeks). A chain of blocks will be pre-generated for each stratum, e.g., 1000 blocks. The size of each block will also be randomly and independently chosen as 2, 4, or 6 individuals. The study will use the tool at sealedenvelope.com to generate the randomization list. The random seed will be generated using the random integer generator at random.org, which introduces randomness from unpredictable atmospheric noise (see more below).

### Concealment mechanism {16b}

Each assignment will be printed and stored in a sealed envelope at the University of Florida, and envelopes will be ordered according to the randomization list in each gestational age group. When a study subject is screened for enrollment and is deemed eligible, she will be offered enrollment and engaged in an informed consent process. If she agrees to participate (and provides consent), she will choose an envelope from among three arranged consecutively, each of which has a piece of paper in it that indicates whether she is in the treatment or control group. The choice of envelope was included with the block design to ensure a sense of autonomy among participants and that they feel able to make a choice. Each subject will have a unique randomization code, in addition to a unique study ID, so that the original assignment of each subject can be easily tracked.

### Implementation {16c}

A biostatistician on the study team ([name]) will generate the allocation sequence and be blinded to the assignment. Study staff who take the informed consent will enroll participants. Separate study staff will be responsible for facilitating each participant’s selection of an envelope and allocation into control or intervention groups.

## Assignment of interventions: blinding

### Who will be blinded? {17a}

Field staff responsible for measuring primary and secondary outcomes and data analysts performing the analysis will be blinded about treatment assignments. Study staff involved in administering informed consent and data collection (except daily compliance) will also be blinded. The assignment envelopes will be pre-filled in advance, and both the study participant and the staff person facilitating this randomization reveal process will be blinded to what is inside the envelope until it is opened. The two primary study analysts responsible for the analysis of the primary outcome and replication will also be blinded until replication has been confirmed.

### Procedure of unblinding if needed? {17b}

Staff conducting data quality checks and staff doing the intervention delivery will only be unblinded to the allocated intervention. All other study staff will remain blinded.

## Data collection and management

### Plans for assessment and collection of outcomes {18a}

At enrollment, an ultrasound screening will be conducted to determine eligibility, followed by a baseline survey on demographic and background characteristics of the household. Questions in the survey will include pregnancy and medical history, maternal behavior towards risk factors (e.g., malaria), physical activity, dietary diversity using the Dietary Quality Questionnaire (DQQ) (Global Diet Quality Project), household food security using the Household Food Insecurity Access Scale (HFIAS) [8], and water and sanitation practices. Women’s anthropometric measurements will be taken using Seca scales, including height (Seca 213 portable measuring rod), weight (Seca 874), and mid-upper arm circumference (MUAC). Blood samples and hair samples will also be collected at baseline.

During two additional clinical visits in the second (20–26 weeks) and third trimester (30–34 weeks), anthropometric measurements (height, weight, MUAC) from all women will be taken, as well as blood and hair samples. Ultrasound measurements will also be taken to assess fetal growth measures that include biparietal diameter, head circumference, abdominal circumference, and femur length. Information on medical conditions since the last visit, depression screening using the Edinburgh Postnatal Depression Scale (EPDS), physical activity, breastfeeding intention, consumption and preparation recall of CSB+, and maternal diet (DQQ) will be collected using a short survey during these visits.

At birth, anthropometric measurements of all neonates will be assessed twice within 72 h after birth, with the first 24 h as the target window. A third measurement will be taken in case of discrepancies between the first two measurements. For recumbent length, a third measurement will be taken if the difference between the first two measurements is more than 0.7 cm. A third weight measurement will be taken in case the difference in the weight in the first two measurements is more than 10 g. Length measurements will be taken using length board S0114540 set3, and weight will be measured using Seca 334 scale.

After birth, the mother and child will be asked to engage with study staff for additional assessments during the child’s routine health exams at 6 weeks and 6 months of age. At each of these visits, the mother will answer survey questions including the DQQ adapted for Rwanda [19], infant feeding practices, and whether the infant is exclusively breastfed [52]. The questionnaire will use WHO-recommended core indicators [52] of optimal breastfeeding that include early initiation of breastfeeding (within 1 h of birth) and exclusive breastfeeding until 6 months after birth. A survey module on the infant’s health and morbidity (caregiver-reported diarrhea, respiratory issues, fever, malaria) and care-seeking behavior will also be administered. If consented and pending funding availability, medical records at health facilities (outpatient, integrated management of childhood illness (IMCI), inpatient) and CHW sick child encounter forms will be extracted to understand the impacts of the nutrition interventions on child health outcomes, including diarrhea, respiratory infections, fever, and malaria, as well as mortality. The study team will also administer survey questions regarding exposure to gender-based violence (using questions from the Demographic Health Surveys).

At birth, 6 weeks, and 6 months of age, the child’s recumbent length will be measured twice using length boards to the nearest 0.1 cm. Weight will be measured to the nearest 0.1 kg using a digital scale (Seca 334). A third measurement will be taken in case of discrepancies between the first two measurements. For length, a third measurement will be taken if the difference between the first two measurements is more than 0.7 cm. A third weight measurement will be taken in case the difference in weight between the first two measurements is more than 10 g. The two most approximate readings will be averaged for analysis. Head circumference of the infant will be measured to the nearest 0.1 cm using a standard, non-stretchable measuring tape, ensuring accurate and consistent placement around the largest part of the infant’s head (above the eyebrows and ears and around the back of the head) for reliability across measurements. MUAC will also be assessed at 6 months of age using a calibrated, non-stretchable measuring tape placed around the mid-upper arm at the midpoint between the shoulder and elbow, with measurements recorded to the nearest 0.1 cm to monitor nutritional status, and referrals will be made for those classified as moderate or severe acute malnutrition.

Additionally, at 6 weeks of age, infants will be assessed for neurodevelopment using the Hammersmith Neonatal Neurological Examination (HNNE) for newborn development assessment and at 6 months using the Caregiver Reported Early Development Instruments (CREDI), a validated assessment tool [51] used previously in Rwanda [7]. The CREDI (long form) provides domain-specific scores in motor, cognitive, language, and social-emotional development, as well as an overall score. Blood will be drawn from both the mother and the infant at 6 weeks and 6 months and stored as described below. A hair sample from the mother will be requested if consented.

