***Secondary outcomes***					
*** Child outcomes***					
* In-utero measurements*	Head circumference z-scores	Continuous (z-score)	INTERGROWTH 21st growth standards	Between 20–26 weeks and 30–34 weeks of gestational ages	Mean (SD)
	Femur length z-scores	Continuous (z-score)	INTERGROWTH 21st growth standards	Between 20–26 weeks and 30–34 weeks of gestational ages	Mean (SD)
	Abdominal circumference z-scores	Continuous (z-score)	INTERGROWTH 21st growth standards	Between 20–26 weeks and 30–34 weeks of gestational ages	Mean (SD)
	Bi-parietal z-scores	Continuous (z-score)	INTERGROWTH 21st growth standards	Between 20–26 weeks and 30–34 weeks of gestational ages	Mean (SD)
	Estimated fetal weight z-scores	Continuous (z-score)	INTERGROWTH 21st growth standards	Between 20–26 weeks and 30–34 weeks of gestational ages	Mean (SD)
	Cerebellar diameter	Continuous (cm)	Ultrasound measurement	Between 20–26 weeks and 30–34 weeks of gestational ages	Mean (SD)
	Corpus callosum length	Continuous (cm)	Ultrasound measurement	Between 20–26 weeks and 30–34 weeks of gestational ages	Mean (SD)
	Thalamus midline axial	Continuous (cm)	Ultrasound measurement	Between 20–26 weeks and 30–34 weeks of gestational ages	Mean (SD)
	Gangliothalamic ovoid diameter	Continuous (cm)	Ultrasound measurement	Between 20–26 weeks and 30–34 weeks of gestational ages	Mean (SD)
	Gangliothalamic ovoid sagittal length	Continuous (cm)	Ultrasound measurement	Between 20–26 weeks and 30–34 weeks of gestational ages	Mean (SD)
	Gangliothalamic ovoid estimated volume	Continuous (cubic cm)	Ultrasound measurement	Between 20–26 weeks and 30–34 weeks of gestational ages	Mean (SD)
* Newborn measurements*	Small for gestational age (SGA) at birth (< 10th percentile and < 3rd percentile)	Binary (two thresholds)	INTERGROWTH 21st growth standards	Within 72 h of birth	Proportion
	Birthweight for gestational age at birth	Continuous (z-score)	INTERGROWTH 21st growth standards	Within 72 h of birth	Mean (SD)
	Preterm live birth (< 37 weeks completed gestation)	Binary	Delivery < 37 + 0 weeks completed gestation	At birth of newborn	Proportion
	Birthweight (g)	Continuous (in g)	Measured using calibrated scale	Within 72 h of birth	Mean (SD)
	Low birthweight	Binary	Birthweight < 2500 g	Within 72 h of birth	Proportion
	Birth weight-for-age z-score	Continuous (z-score)	INTERGROWTH 21st growth standards	Within 72 h of birth	Mean (SD)

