	Small vulnerable newborn status	Binary	Any of: SGA (< 10th), preterm (< 37 weeks), or low birthweight (< 2500 g)	Within 72 h of birth	Proportion
	Head circumference z-score	Continuous (z-score)	INTERGROWTH 21st growth standards	Within 72 h of birth	Mean (SD)
* Infant measurements*	Prevalence of stunting among infants	Binary	Length-for-age < −2 SD according to the WHO Multicenter Growth Reference Study standards	At 6 weeks and 6 months of age	Percentage
	Infant weight-for-age z score	Continuous (z-score)	WHO Child Growth Standards	At 6 weeks and 6 months of age	Mean (SD)
	Prevalence of underweight	Binary	Weight-for-age < -2 SD according to the WHO Multicenter Growth Reference Study standards	At 6 weeks and 6 months of age	Percentage
	Child neurodevelopment- HNNE	Continuous/domain score	Hammersmith Neonatal Neurological Examination (HNNE)	At 6 weeks of age	Domain and total scores
	Child neurodevelopment-CREDI	Continuous	Caregiver-Reported Early Childhood Development Instrument (CREDI) score (long form)	At 6 months of age	Domain-specific scores

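### The stated 0.1 kg resolution for infant weight contradicts the 10 g repeat rule and, if followed, would under-count low birthweight

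*Protocol article*

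**What the plan says.** All references are to the protocol article.

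- **Resolution.** The paragraph of section {18a} on child measurements opens: "At birth, 6 weeks, and 6 months of age, the child’s recumbent length will be measured twice using length boards to the nearest 0.1 cm". The next sentence reads: "Weight will be measured to the nearest 0.1 kg using a digital scale (Seca 334". It gives no ages of its own, so it is naturally read as covering birth, 6 weeks and 6 months.
- **Repeat rule.** The same paragraph continues: "A third weight measurement will be taken in case the difference in weight between the first two measurements is more than 10 g". The earlier paragraph of {18a} on measurements at birth gives the same threshold: "A third weight measurement will be taken in case the difference in the weight in the first two measurements is more than 10 g". That paragraph names the same scale but no resolution.
- **Value analysed.** "The two most approximate readings will be averaged for analysis".
- **Outcomes.** In Table 1, birthweight is "Continuous (in g)", low birthweight is "Birthweight < 2500 g", and the small vulnerable newborn composite uses the same cut-off: "Any of: SGA (< 10th), preterm (< 37 weeks), or low birthweight (< 2500 g)".

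Nothing in the article reconciles the 0.1 kg step with the 10 g threshold or with outcomes in grams.

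**The concern.** The recording step (0.1 kg = 100 g) is ten times the tolerance it is meant to support (10 g). Both are stated for the same weighings, so the instruction contradicts itself. The length rule in the same paragraph, 0.1 cm steps with a 0.7 cm threshold, has no such problem.

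Two things are at stake if staff or form builders follow the 0.1 kg sentence. The duplicate-weighing check loses most of its ability to detect discrepancies. In addition, the low-birthweight cut-off lies exactly on a grid point, so rounding near it acts in one direction. Weights just under 2500 g move up to 2.5 kg and leave the category, and weights of 2500 g or more do not move below it.

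**Working it through.** The article gives no computed figure on this point, so there is none to reproduce. From the article come the 100 g step, the 10 g threshold, the 2500 g cut-off, the averaging rule, 956 women and 20% attrition. It does not give the birthweight mean and SD or the reading error. These are assumed below, with ranges.

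**1. What the repeat rule becomes.** Recorded pairs can differ only by 0, 100, 200 g and so on. More than 10 g therefore means 100 g or more, and a third weighing occurs exactly when the two recorded values are not identical. A simulation of 1,000,000 pairs per row (weights with mean 3000 g, SD 450 g) gives:

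| Assumed reading-error SD | Pairs truly differing by > 10 g | Of those, flagged on a 100 g grid |
|---|---|---|
| 5 g | 16% | 13% |
| 10 g | 48% | 18% |
| 20 g | 72% | 29% |
| 50 g | 89% | 57% |

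For error SDs of 5–50 g, about 4–5% of pairs that truly agree within 10 g are also flagged. That costs only an extra weighing.

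**2. Low birthweight.** A true weight in 2450–2499 g rounds to 2.5 kg, which is not below 2500 g. The effective cut-off becomes 2450 g.

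- True proportion: Φ((2500 − μ)/σ)
- Recorded proportion: Φ((2450 − μ)/σ)

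At μ = 3100 g, σ = 450 g: Φ(−1.333) = 0.0912 and Φ(−1.444) = 0.0743. Share missed: (0.0912 − 0.0743)/0.0912 = 18.5%.

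Share of low-birthweight infants missed, varying both inputs:

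| Mean | SD 420 g | SD 450 g | SD 500 g |
|---|---|---|---|
| 3000 g | 18.6% | 16.8% | 14.5% |
| 3100 g | 20.5% | 18.5% | 15.9% |
| 3200 g | 22.4% | 20.2% | 17.3% |

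The range is about 14–22%. As a share of all births it is 1.1–2.3%. After 20% attrition 956 × 0.8 ≈ 764 births remain, so this is about 8–18 infants.

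**3. Does averaging rescue it?** Averaging two 0.1 kg readings without the third weighing lowers the loss slightly: at mean 3000 g, SD 450 g, from 16.8% to 13–16% for reading-error SDs of 3–20 g. Under the full rule, any disagreement brings a third reading, and the two closest readings are then normally identical on the grid. Simulating that at 3100/450 g leaves the loss at 18–19% for the same error SDs.

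**4. Mean birthweight.** Rounding to 100 g adds an error SD of 100/√12 ≈ 29 g. The variance rises by (100²/12)/450² ≈ 0.4%, which is negligible.

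**5. With a 10 g step.** Only true weights of 2495–2499 g would round up to 2500 g. Over the same inputs that is about 1.5–2.5% of low-birthweight infants.

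**The case against.** The strongest reply is that 0.1 kg is simply a slip. The 10 g rule appears twice, birthweight is an outcome in grams, and the birth-specific paragraph names the scale without any 0.1 kg step. All of that suggests that weights are in fact taken more finely. This stands in part. The contradiction is certain but the misclassification is conditional, because the article gives neither the scale's resolution nor the format of the data-capture field. A slip in a measurement instruction still has to be corrected, since people may work from it.

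A reader might go further and infer three things that the article does not support.

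- **That the repeat rule does not function at all.** It still triggers third weighings. What is lost is the 10 g tolerance and, with moderate reading error, most of the sensitivity.
- **That the comparison between arms is biased.** The rounding applies to both arms and amounts to a cut-off of 2450 g. As an illustration with means of 3100 and 3150 g and SD 450 g, the true risks are 9.1% and 7.4% and the recorded risks 7.4% and 6.0%. The risk ratio is 0.81 either way, and the difference shrinks from 1.7 to 1.4 percentage points.
- **That all weight-based outcomes are distorted in the same way.** The cut-offs for small for gestational age and underweight vary with age and sex and do not sit on a fixed grid point, so rounding errors there have no fixed direction and are not quantified here. In the small vulnerable newborn composite, a missed infant is still counted if preterm or small for gestational age, so the loss is smaller than for low birthweight alone.

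**Conclusion.** The contradiction holds as a matter of the text: a 0.1 kg step and a 10 g tolerance cannot both govern the same weighings. If the 0.1 kg sentence is followed, low birthweight is under-counted by about 14–22% of cases, assuming approximately normal birthweights with mean 3000–3200 g and SD 420–500 g. The result would be an understated prevalence and some lost information, with neither arm favoured. Mean birthweight is barely affected. The primary outcome, length-for-age z-score at birth, does not use weight and is untouched. This is a minor point, confined to secondary outcomes, and worth correcting because the correction is so cheap.

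**What to change.** Correct the sentence in {18a} so that child weight at birth, 6 weeks and 6 months is recorded in grams, at a resolution no coarser than the 10 g repeat threshold, and keep the 10 g rule. A step finer than 10 g, if the scale shows one, serves the rule better: in the simulation above with a reading-error SD of 10 g, a 10 g grid flags 62% of true differences above 10 g and a 5 g grid 79%, against 18% on the 100 g grid.

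Check that the REDCap weight field holds grams at that resolution. If any weights were stored only to 0.1 kg, recover the original readings where they exist, flag the rest, and report low birthweight with those records identified.

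The cost is one sentence, a check of one form field and a note to measurers, with the same scale and visits. The article reports that enrollment is paused, so the correction can be in place before it resumes.
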